**Fig. 3 Fig3:**
[figure not shown]
Flowchart. *Green boxes* indicate assessment of remission. *Brown boxes* indicate medication dosage-related events (maintaining, intensifying, and tapering treatment). *Red boxes* indicate patient dropouts. *Blue diamonds* indicate decisions for patient-tailored treatment. *Orange boxes* refer to current medication dosages. *Clinical remission* is remission according to ACR/EULAR 2011 Boolean remission criteria [10]. *HandScan remission* remission is achieved if total optical spectral transmission (OST) score ≤ 11 AND a maximum of one joint with OST > 1. *MTX* methotrexate, *LEF* leflunomide, *PRED* prednisolone, *HCQ* hydroxychloroquine, *aTNF* tumour necrosis factor inhibitor, *MTX at max* maximum (tolerable) dose, i.e., 30 mg or lower, or maximal tolerable dose, *AE* adverse event or effect, *ML* medication level

### Adverse reactions to DMARDs

In case of adverse reactions to initial dose of MTX (10 mg/week), MTX will be substituted with leflunomide (LEF) 20 mg/day. If LEF is well tolerated and remission is not achieved, HCQ will be added; next escalation steps are as described above (Table 2). Patients that switch to LEF and are consequently unable to achieve remission will reach anti-TNF treatment faster than patients on MTX (with the exception of an MTD). In case of adverse reactions to MTX at dosages ≥ 10 mg/week, the last well-tolerated dose will be administered subcutaneously and considered to be the MTD. If remission is not achieved, treatment will be intensified according to Table 2, e.g., at a MTD of MTX 15 mg/week subcutaneously, HCQ will be added.

### Implementation of a software application for patient-tailored, tight-control treatment

Although treatment regimens and dosing steps are identical for all patients, actual medication will differ considerably between patients in this study, as the study protocol tailors treatment to every patient in a treat-to-target strategy (Fig. 3). To account for these variations in treatments and to allow for double-blind treatment, a decision-making software application was developed. It uses a data trail (data log) of current and previous patient-specific input to check, e.g., for consistent discordance between remission criteria and prevent drug dosages higher than previous MTD in case of a flare. At each visit, the patient identification number, year of birth, and parameters for both clinically and HandScan-assessed disease activity will be entered into the application. Based on whether there is remission or not, according to the criteria of the randomized arm, the application will provide the next patient-specific medication step.

The application was developed and tested to conform to the regulations and guidelines for the development of a medical appliance class I and medical software class B (*EN 62304 Medical device software –Software life-cycle processes, EN 62366 Usability, ISO 14971 Medical devices – Application of risk management to medical devices*).

### Prevention of under- and overtreatment in the HandScan arm

Since treatment guidance by the HandScan is a novel approach, measures are taken to prevent large deviation of the HandScan-guided strategy from the DAS guided strategy to avoid under- or overtreatment. If treatment decisions dictated by HandScan at three consecutive monthly visits (Fig. 3) are discordant with decisions that would have been dictated by DAS, patients will be switched to the DAS-guided arm and medication decisions will be immediately guided by this arm. Discordancies are tracked in the software application; the switch is implemented without intervention of the researcher, blinded for researcher and patient. This way, patients in the HandScan arm might potentially be under- or overtreated (based on DAS guidance) only for a maximum of two consecutive months.

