### Treatment strategy

After randomization, in both arms all patients will initiate a methotrexate (MTX)-based tight-control strategy, with 10 mg per week MTX orally as starting dose and with prednisolone (PRED) fixed dose of 10 mg/day orally [15]. Patients are evaluated monthly and at each visit a dosage decision is made based on efficacy and adverse events. In case remission is not achieved, MTX dose will be increased at each monthly visit until either remission or the maximum tolerable dose (MTD) is reached (Table 2). Escalation steps are 15, 20, 25, 30 mg MTX/week orally, followed by 30 mg MTX/wk (or MTD) subcutaneously. At a dose of MTX of 25 mg/week (or MTD of MTX), hydroxychloroquine (HCQ) 400 mg/day for patients ≥ 60 kg (or 200 mg/day for patients ≤ 60 kg) will be added. After the final escalation step of MTX, in case of no remission, tumor necrosis factor inhibitor (anti-TNF), e.g., adalimumab 40 mg s.c. every 2 weeks, will be added to the MTX therapy, while HCQ will be stopped.

**Table 2 Tab2:** Intensifying treatment strategy in case remission is not achieved

Week	MTX*	PRED	HCQ	Anti-TNF
	mg/week	10 mg/day	400 mg/day	
0 = start of study	10	+	–	–
+ 4	15	+	–	–
+ 4	20	+	–	–
+ 4	25	+	+	–
+ 4	30	+	+	–
+ 4	Same dose s.c.	+	+	–
+ 4	Same dose s.c.	+	–	+
+ 4	Same dose s.c.	+	–	+
+ 4	Same dose s.c.	+	–	+

If remission is not achieved after each period of 4 weeks, treatment is intensified stepwise. *MTX* methotrexate, *PRED* prednisolone, *HCQ* hydroxychloroquine, *anti-TNF* anti-tumor necrosis factor, *s.c.* subcutaneously

*Same dose s.c.: the dose at the previous step, given s.c. at a dose of 30 mg, or earlier. In case of dose-dependent adverse reactions to MTX (> 10 mg/week), previously tolerated dose will be administered s.c., and this will then be the maximum tolerable dose (MTD) for that patient. Further intensifying treatment would be adding or continuing HCQ. HCQ is given for three consecutive months in every scenario

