### Patient safety

An independent researcher will analyze the number of study arm switches when the first 20 patients have 6 months of follow-up data. If more than ten patients need to switch to the DAS-guided arm because of discordant treatment decisions for three consecutive months, inclusion will be stopped. The patients who have been included up to that moment will continue to be followed-up, to obtain sufficient information for the evaluation of the HandScan functionality in tight-control treatment strategy. If more than 20% of the first 20 patients have protocol violations based on clinical judgment within 6 months after inclusion, the medical research ethics committee (MREC) will be informed and protocol modifications deemed necessary will be communicated with the site investigators, treating rheumatologists, and, if necessary, trial participants. All adverse events reported by trial participants or observed by investigator staff will be recorded. As the study does not involve experimental medication or treatment, no safety analysis will be performed and an independent data safety and monitoring board will not be installed.

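### The three-visit switch rule caps consecutive discordant decisions at two; it does not cap under- or overtreatment at two months, as the protocol states

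*Protocol article*

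**What the plan says.** The section on prevention of under- and overtreatment in the HandScan arm gives the rule and its claimed effect. The trigger is: "If treatment decisions dictated by HandScan at three consecutive monthly visits (Fig. 3) are discordant with decisions that would have been dictated by DAS". The consequence is: "patients will be switched to the DAS-guided arm and medication decisions will be immediately guided by this arm". The section concludes that HandScan-arm patients "might potentially be under- or overtreated (based on DAS guidance) only for a maximum of two consecutive months".

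Three other sections determine what the rule does to treatment:

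- **Software application.** The data log is used to check "for consistent discordance between remission criteria and prevent drug dosages higher than previous MTD in case of a flare". At each visit "the application will provide the next patient-specific medication step".
- **Treatment strategy.** "Patients are evaluated monthly and at each visit a dosage decision is made based on efficacy and adverse events". The note to Table 2 adds: "If remission is not achieved after each period of 4 weeks, treatment is intensified stepwise". De-escalation is slower: one step once remission has lasted three months, then one more for each further 3 months, with prednisolone always first.
- **Patient safety.** "An independent researcher will analyze the number of study arm switches when the first 20 patients have 6 months of follow-up data". More than ten switches stops inclusion. A second trigger concerns protocol violations, judged clinically, in more than 20% of the first 20 patients. Adverse events are recorded, but no safety analysis is planned and there is no data safety and monitoring board.

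**The concern.** The sentence sets a maximum on how long a patient can be treated too little or too much by the DAS standard. The rule acts on something else, namely whether the two methods point to different decisions at a given visit. Treatment is cumulative: a step withheld at one visit is still missing at the next, even if every later decision follows DAS. The text describes no way of making up missed steps, or of quickly removing extra ones, after a switch or a concordant visit.

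The sentence is an assurance about a new guidance method. An ethics committee, a site or a later reader would take it as a property of the design. If the rule does not deliver it, the final report would overstate the protection, and an early review of switches would not reveal the difference.

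**Working it through.** **Inputs.** Switch at the third discordant visit in a row (section on under- and overtreatment); one escalation step per 4-weekly visit and six steps from start to anti-TNF (Table 2); one de-escalation step per 12 weeks (Table 3); 18 months of follow-up, counted as 18 monthly visits.

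**1. The protocol's own figure.** At the third discordant visit the DAS decision applies, so the longest run of discordant decisions acted on is 3 − 1 = 2, or two monthly intervals. The stated two months reproduces in this sense only.

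**2. Undertreatment when the rule works as written.** Number the steps of Table 2 from 0 to 6: methotrexate 10; 15; 20; 25 + HCQ; 30 + HCQ; s.c. + HCQ; s.c. + anti-TNF. Take a patient who is never in DAS remission but whom HandScan classes as in remission at months 1, 2 and 3.

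- DAS-guided step at month m: min(6, m).
- Actual step: 0 at months 1 and 2 (held), then one step per visit from the switch at month 3, so min(6, m − 2).

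| Month | 1 | 2 | 3 | 4 | 5 | 6 | 7 | 8 |
|---|---|---|---|---|---|---|---|---|
| DAS-guided step | 1 | 2 | 3 | 4 | 5 | 6 | 6 | 6 |
| Actual step | 0 | 0 | 1 | 2 | 3 | 4 | 5 | 6 |
| Steps behind | 1 | 2 | 2 | 2 | 2 | 2 | 1 | 0 |

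The patient is behind at months 1 to 7, that is 7 consecutive months (7 × 4 = 28 weeks), and reaches the anti-TNF step at month 8 instead of month 6. With L one-visit steps left on the ladder instead of six, the same arithmetic gives L + 1 months, so a shorter ladder gives a shorter lag.

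**3. The same lag without a switch.** If the patient is discordant at months 1 and 2 only and concordant from month 3, the actual steps are identical. The lag is again 7 months, and there is no switch to count.

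**4. Overtreatment.** Suppose HandScan adds two methotrexate steps (10 to 15 to 20) that DAS would not have added, and remission then persists. Under Table 3 the prednisolone step comes first (12 weeks), then 20 to 15 (12 weeks), then 15 to 10 (12 weeks): 12 + 12 + 12 = 36 weeks from the last extra step. Even a single de-escalation step takes 12 weeks, longer than two months.

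**5. Non-consecutive discordance.** A repeating pattern of two discordant visits and one concordant visit never gives three in a row. Over 18 visits it gives (18 ÷ 3) × 2 = 12 discordant visits with no switch; full enumeration confirms 12 as the maximum. Over the first six visits, the window of the early review, the maximum is 4.

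**The case against.** **The sentence says consecutive.** Read as covering unbroken runs of discordant decisions, two is correct. This stands as far as recurrence goes: a reader might infer from the 12 of 18 visits that the sentence is false on that account, and it is not, because a cumulative count does not contradict a consecutive bound. But the 7-month lag is itself consecutive, and the sentence speaks of being under- or overtreated.

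**The protocol compares decisions, not levels.** After a switch, each new decision is the one DAS dictates from the patient's current step, so one can argue that the patient is then treated according to DAS. That reading is possible, but under it the sentence should refer to decisions.

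**Fig. 3 was not available.** It is cited at exactly this rule, and its legend mentions medication levels. A catch-up step there would change the result. The text sets out escalation, flare, maximum tolerable dose and leflunomide rules in detail and mentions none.

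**The 7 months is a worst case.** It needs a patient never in DAS remission, the full ladder, and discordance at the first three visits. A maximum tolerable dose or leflunomide shortens it. All of this stands, but a stated maximum is a worst-case claim, and one path that complies with the rule is enough to exceed it.

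**How many patients are affected?** A reader might infer that most HandScan-arm patients would exceed two months. The documents do not support any such percentage. They give no discordance rate, and the answer depends strongly on whether discordance persists within a patient. Persistent discordance is what the rule catches.

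**Is discordance unmonitored?** A reader might also infer this. It is not: the software tracks discordances, both measures are taken monthly, and the protocol-violation trigger is a second check. That trigger does not, however, measure discordance or lag, since following HandScan is compliance with the protocol.

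**Conclusion.** The point holds as a mismatch between a stated safety property and the rule meant to deliver it. The rule guarantees at most two consecutive discordant decisions. It does not guarantee at most two months at a different treatment step: on the protocol's own ladder the worst case is about 7 months and up to two steps behind, and for overtreatment about 36 weeks in the example above. Both figures assume no catch-up step in Fig. 3; the first also assumes the full methotrexate ladder, and the second that remission persists. No discordance rate is needed.

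The absence of a limit on non-consecutive discordance is a separate limitation, not a contradiction. It matters because neither this pattern nor the lag would show in the independent researcher's count of switches. Sample size and primary analysis are unaffected. The sentence should be corrected, because it overstates the protection given.

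**What to change.** Reconcile the section on under- and overtreatment with the treatment strategy (Tables 2 and 3) and the software section. State the bound as what the rule delivers: at most two consecutive discordant decisions are acted on, with no stated limit on cumulative discordance or on the resulting difference in treatment step. If Fig. 3 does contain a catch-up step, describe it in the text and derive the bound from it.

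Have the existing review of the first 20 patients, and the final report, also tabulate two quantities per patient from the software log: the cumulative number of discordant decisions, and the time at a treatment step other than the one DAS would have dictated. These would stand beside the count of switches and the protocol-violation trigger.

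The cost is one reworded sentence and one additional table, from inputs already entered and discordances already tracked. The downside is that the stated safety assurance becomes weaker. No change to the switch rule or to any dosing rule is proposed; that is for the clinical investigators.

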### Statistical analyses

#### Sample size

Sample size was calculated for the primary outcome, HAQ score, and the primary analysis of the non-inferiority design using two-sample *t*-tests and data from the CAMERA-II trial: mean (SD) HAQ score at 18 months 0.38(0.4) [15]. An equivalence margin of 0.2 in HAQ scores between study arms was considered clinically acceptable. A sample size of 51 per group was calculated to obtain a power of 80% at a one-sided *p* value of 0.05. Taking into account 10% drop-out, total sample size was set at 112 patients.

#### Primary outcome analyses

The primary outcome is HAQ score; the primary analysis is a general linear model, testing HAQ scores at 18 months between the two arms according to intention to treat (ITT), controlling for baseline HAQ, center (stratification factor in the randomization), and the baseline covariates age, gender, disease activity (DAS28), rheumatoid factor, and anti-CCP. The ITT population will include all randomized patients as long as they have taken study medication at least once and at least one efficacy measurement was obtained. Secondary analyses are 1) the primary analysis, but for the per protocol population (i.e., all patients without major protocol violations or a switch between study arms), and 2) a mixed model analysis comparing HAQ scores over time (baseline and 3, 6, 12, and 18 months) between the study arms. In this model we will control for the same covariates as those in the primary analysis. Although this model handles missing data well, if ≥ 10% of data are missing, as a sensitivity analysis data will be analyzed after multiple imputation if data seem to be missing at random.

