## Methods/design

This is an investigator-initiated, multi-center, double-blind non-inferiority randomized controlled trial (RCT) of 18 months duration. Patients will be randomized (1:1) to a HandScan-guided treatment aimed at HandScan remission (HandScan arm) or a clinically DAS-guided treatment aimed at ACR/EULAR 2011 Boolean remission (DAS arm). The study is performed at six departments of rheumatology in the Netherlands, the University Medical Center Utrecht (UMCU), and five non-university hospitals: Meander Medical Center Amersfoort, Noord West Ziekenhuizen Alkmaar, Máxima Medisch Centrum Eindhoven, and Gelre Ziekenhuizen Apeldoorn. The study has been approved by the Ethical Committee of the University Medical Center Utrecht, Utrecht, The Netherlands on April 6, 2017 (NL50026.041.14), and has been registered in the Dutch Trial Register (NTR6388). Privacy of patients will be protected according to the General Data Protection Regulation, using anonymized data.

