### Assessments

Patients will visit the outpatient clinics monthly (Fig. 1). At each visit, disease activity will be measured, to ensure blinding both with HandScan and DAS44, consisting of serum CRP, a 44 joints assessment for swelling and tenderness, and a PGA (VAS 0–10 cm, 10 = worst). At baseline and 3, 6, 12, and 18 months patients will fill out the HAQ (first outcome), the Short Form Health Survey (SF36), EuroQol (EQ5D), and the questionnaire on direct and indirect costs (second outcome). Direct costs (health care) and indirect costs (loss of paid and household productivity) will be calculated from questionnaires, including the Health and Labour questionnaire [13]. Radiographs in the antero-posterior direction of hands, wrists, and feet will be obtained at baseline and 18 months (second outcome). The current gold standard for scoring these radiographs is the Sharp/van der Heijde scoring method [11]. This method scores erosions (score 0–5 per region) and joint space narrowing (score 0–4 per region) of these joints and sums the scores to the SHS score, ranging from 0 to 448. A newly developed fully automated radiographic scoring system of hand and wrist joints is also applied to quantify changes in the joint space width over time.

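### The primary ITT model of the 18-month HAQ is in effect complete-case; the all-visit mixed model is only secondary, and imputation depends on an unverifiable judgement about missingness

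*Protocol article*

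**What the plan says.** Under Primary outcome analyses, the Protocol article defines the primary analysis as "a general linear model, testing HAQ scores at 18 months between the two arms according to intention to treat", adjusted for baseline HAQ, center and further baseline covariates. The ITT population is all randomized patients "as long as they have taken study medication at least once and at least one efficacy measurement was obtained". An 18-month HAQ is not a condition of membership, and nothing is said about how the primary model treats a patient without one.

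The Assessments section schedules the outcome repeatedly: "At baseline and 3, 6, 12, and 18 months patients will fill out the HAQ". The intermediate visits are used in a secondary analysis, "a mixed model analysis comparing HAQ scores over time (baseline and 3, 6, 12, and 18 months) between the study arms", with the same covariates.

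The text then remarks that this model copes well with missing data. It adds that, once at least 10% of data are missing, "as a sensitivity analysis data will be analyzed after multiple imputation if data seem to be missing at random". Under Secondary outcomes, by contrast, multiple imputation for costs and QALYs is stated without either condition.

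**The concern.** The population and the model do not match. A linear model with the 18-month HAQ as its response can use only patients who have that value. The analysis labelled ITT therefore covers completers, and the 3-, 6- and 12-month HAQ of the others is set aside in the analysis that decides the trial.

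The imputation rule is also poorly framed. Observed data cannot establish that values are missing at random. If the analyst doubts that assumption, the rule removes the sensitivity analysis at the moment it is most needed. If the analyst accepts it, imputation largely repeats what the mixed model already assumes. Neither branch examines a departure from missing at random.

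This matters because the trial tests non-inferiority. If patients with poor function leave the HandScan arm more selectively than the DAS arm, the completers look too similar and the error favors the conclusion the trial hopes to reach.

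**Working it through.** **Inputs from the Protocol article.** Margin 0.2 HAQ; SD 0.4 at 18 months; 51 per group; 10% dropout; 112 patients in total (Sample size); 1:1 allocation (Methods/design); five HAQ visits (Assessments).

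**The plan's own figure.** The normal approximation gives n per arm = 2 × (1.645 + 0.842)² × 0.4² / 0.2² = 49.5, so 50. The exact t-based calculation gives 51 (power 80.6%), which matches. For dropout, 51 × 1.1 = 56.1, or 56 per arm and 112 in total. Dividing by 0.9 gives 57 per arm and 114, which is close.

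**Patients lost to the primary model.** 0.10 × 112 = 11.2, so about 11, taking a dropout to have no 18-month HAQ. Power is not the issue: 56 × 0.9 = 50.4 completers per arm still give about 81%. The issue is bias.

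**Whether imputation would be triggered.** The base of the 10% threshold is not given. Over month-18 values, 11/112 = 9.8%. If only the month-18 form is missing, then over all five scheduled forms 11/(5 × 112) = 2.0%. At the planned dropout the threshold may not be reached, even before missing at random is judged.

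**Size of the bias, by simulation.** The assumptions below are not document figures, except the SD and the 56 per arm:
- true difference 0.20 at every post-baseline visit;
- correlation 0.6 between post-baseline visits and 0.4 with baseline;
- dropout before month 18 by a logistic model in the month-12 HAQ, with log-odds slope 0.5 to 1.5 per SD.

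The complete-case linear model adjusted for baseline HAQ was compared with filling in the 18-month value from baseline and the 3-, 6- and 12-month HAQ.

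| Dropout HandScan/DAS | What drives it | Complete-case | Using earlier visits |
|---|---|---|---|
| 10%/10% | HAQ in HandScan arm, random in DAS arm | 0.18-0.19 | 0.20 |
| 20%/10% | HAQ in HandScan arm, random in DAS arm | 0.16-0.18 | 0.20 |
| 10%/10% | HAQ in both arms | 0.20 | 0.20 |

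Against the 0.2 margin, the shift is 0.01-0.02 (5-10%) in the first row, 0.02-0.04 (10-20%) in the second and nil in the third.

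**Departure from missing at random.** Suppose a fraction f of the HandScan arm is missing and those patients are worse by d than the analysis predicts. The difference is then understated by f × d: 0.10 × 0.2 = 0.02, 0.10 × 0.4 = 0.04, 0.20 × 0.4 = 0.08. Both d and the 20% are illustrative, and d = 0.4 is a full SD. No planned analysis of the HAQ explores this quantity.

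**The case against.** A reader might infer that dropout bias is neither reduced nor tested, or that no planned analysis could reveal it. The document does not support that. The mixed model over all HAQ visits is unconditional, uses patients who lack the 18-month value, and reduces dropout bias under missing at random. Set beside the primary result, it could expose the gap shown above. What remains is that it is secondary, is described as a comparison over time without a named 18-month contrast, and so does not carry the non-inferiority conclusion.

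A reader might also take the bias as likely. It needs dropout that differs between arms in cause or rate, and the design works against that: patients and site staff are blinded to the guidance method, drugs and steps are identical, and persistently discordant HandScan patients are moved to DAS guidance without anyone knowing. The plan gives no reason to expect unequal dropout. This objection stands as a limit on the size, and the 20%/10% row doubles the planned rate in one arm.

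The imputation sentence follows the remark about the mixed model but does not say which model is refitted, so it cannot be said to exclude the primary model.

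Finally, this is a condensed article, and further missing-data detail may sit in the full protocol or SAP. That would excuse silence. It does not cover the primary model, the population rule and the condition on imputation, all of which the article states.

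**Conclusion.** The point holds in a limited form. As written, the primary analysis is complete-case under an ITT label, and about 11 of 112 patients would not contribute at the planned dropout. The analysis that uses their earlier HAQ has only a secondary role. Imputation depends on two conditions, one of which cannot be verified, and nothing examines departures from missing at random.

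The numerical effect is conditional. With a true difference at the margin, the complete-case estimate falls by about 0.01-0.02 at 10% dropout per arm if only HandScan dropout follows HAQ, by 0.02-0.04 at 20% versus 10%, and not at all if cause and rate are the same in both arms. These figures rest on the assumed correlations, slopes and dropout patterns. They show what could happen, not what is expected. The change should be made because a better analysis is already in the plan.

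**What to change.** 1. Make the 18-month arm contrast from the mixed model the primary analysis, with the 3-, 6-, 12- and 18-month HAQ as responses and baseline HAQ as a covariate. Alternatively, keep the linear model as primary but impute the 18-month HAQ from the earlier visits, whatever the amount of missing data.
2. Keep the complete-case linear model as a supportive analysis.
3. Remove the condition that data seem missing at random. In its place, specify a delta-adjusted (tipping-point) analysis that is always run: worsen the imputed HandScan-arm HAQ in steps, and report the step at which non-inferiority is lost so that its plausibility can be judged.

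The cost is revised wording and a few hours of programming. No new data, visits or patients are needed, because the mixed model and all HAQ assessments are already planned.

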### Objectives and primary and secondary outcomes and their rationale

The overall aim of the study described in this protocol is to demonstrate clinical efficacy and cost-effectiveness of the HandScan arm compared to the DAS arm, with identical treatment and treatment steps in both arms. The primary outcome is the change in Health Assessment Questionnaire (HAQ) score from baseline to 18 months, reflecting both actual disease activity and physical disability as a measure for cumulative past disease activity [8]. We chose not to use DAS remission or the Boolean remission criteria with the components of DAS as primary outcome, first, because this would probably favor the DAS arm of our trial over the HandScan arm and, second, because DAS-based remission criteria have a relatively high risk of false negative classification of remission. This is caused by high scores on PGA and TJC in case of concomitant soft tissue rheumatism, fibromyalgia, or other non-inflammatory pain of chronic pain syndrome [9].

Secondary outcomes are the change in HAQ score over time, cost-effectiveness, based on customized cost questionnaires (including direct and indirect costs), and radiographic damage of hand and wrist joints, assessed using a newly developed fully automated radiographic scoring system of joint width of hand and wrist joints [10], as well as the conventional Sharp van der Heijde (SvdH) score of joint width and erosions of hands, wrists, and feet [11].

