## Discussion

This study aims to evaluate clinical efficacy of a HandScan-guided versus DAS-guided tight-control and treat-to-target treatment strategy for early RA. The HandScan guidance has potential drawbacks, mainly because it relies solely on arthritic activity in hands and wrists. However, optical spectral transmission (OST) did correlate to DAS28 in a previous study [6], as well as to US assessed synovial inflammation of hand and wrist joints, while DAS28 did not correlate with these US results. It is possible that, considering the strengths and weaknesses of both guidance methods, the optimal guidance for future treatment of early RA would be using both methods or a combination of parameters of both methods (e.g., HandScan with CRP measurement).

An economic evaluation of guidance of a tight-control strategy using the HandScan has been previously published [17]. Implementation of the HandScan as a monitoring tool was modeled at comparable costs and comparable effects as using clinical assessments. To validate this result, cost-effectiveness in the current study will be calculated based on actual data (i.e., a trial-based economic evaluation); this approach requires less assumptions and therefore has a lower risk of bias.

This protocol describes a specifically designed software application to allow for double-blind, safe, and patient-tailored guidance of treatment. Implementation of the software application has the advantage that it allows for on-site patient randomization and double-blind (for the guidance method) treatment. Deviation from standard treatment schedules is allowed, for example, by defining a MTD or the opportunity to switch from MTX to LEF in case of MTX intolerance. Three consecutive discrepancies in medication advice between the HandScan and DAS arm lead to switch of the respective patients in the HandScan arm to the DAS arm as a built-in safety for potentially large differences between arms. Importantly, as neither the patient nor the physician is aware of a switch, the double-blind design will be maintained.

This specifically designed decision-making software application also allows for implementation of other RCTs testing future, novel methods of guidance of tight-control and treat-to-target treatment strategies in RA.

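### The per-protocol set drops switched patients from the HandScan arm only, so it is a selective comparison of unknown direction and cannot serve as a check on the ITT result

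*Protocol article*

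**What the plan says.** The article's section on prevention of under- and overtreatment sets the switch rule. After three consecutive monthly visits at which the HandScan decision disagrees with the one DAS would have given, "patients will be switched to the DAS-guided arm and medication decisions will be immediately guided by this arm". The software does this automatically and blinded. The Discussion confirms the direction: repeated discrepancies "lead to switch of the respective patients in the HandScan arm to the DAS arm as a built-in safety". No rule moves a DAS-arm patient to HandScan guidance.

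Under Primary outcome analyses, the primary analysis is ITT on 18-month HAQ. It covers all randomized patients with at least one dose and one efficacy measurement. The first secondary analysis repeats it in the per-protocol population, "all patients without major protocol violations or a switch between study arms". The other secondary analysis, a mixed model over time, makes no provision for switching.

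Under Assessments, HandScan and DAS44 are both measured at every monthly visit in both arms.

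**The concern.** In a non-inferiority trial the per-protocol analysis is normally read beside ITT, because ITT can hide a difference when patients do not stay on their assigned strategy. Here the per-protocol set is itself distorted. Switching happens after randomization and depends on disease-activity data, which are related to HAQ. Excluding switchers takes such patients out of the HandScan arm, while DAS-arm patients with the same run of discordant visits stay in. Adjusting for baseline covariates does not restore the balance.

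ITT counts DAS-guided switchers as HandScan patients. That is correct for the strategy actually randomized, which includes the override. However, the Abstract and the opening of Methods/design put the question as HandScan-guided treatment aimed at HandScan remission and do not mention the override. For that question, ITT shrinks any deficit.

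At stake is whether two agreeing analyses would support the claim a reader takes from the trial.

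**Working it through.** **Inputs from Sample size.** The margin is 0.2 ("An equivalence margin of 0.2 in HAQ scores between study arms was considered clinically acceptable"), the SD is 0.4, and there are 51 evaluable patients per group for "power of 80% at a one-sided *p* value of 0.05".

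**Plan's own figure.** With no true difference, SE = 0.4 × √(2/51) = 0.0792 and 0.2/0.0792 = 2.52. The noncentral t-test gives 79.9% power at 50 per group and 80.6% at 51, so 51 reproduces.

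**Assumptions.** The documents give no expected switch share *s*, so I use 10% to 50% of the HandScan arm. The only related figure, under Patient safety, stops inclusion if more than ten patients need to switch when the first 20 have 6 months of follow-up. With 1:1 allocation about ten of those 20 are in the HandScan arm, so the rule hardly bounds *s*. The calculation is an unadjusted t-test.

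**ITT, read as a statement about HandScan guidance alone.** Let the true deficit be δ = 0.2 and let switching restore a share *r* of it. The ITT difference is then δ × (1 − s × r). For example, at s = 30% and r = 1 it is 0.2 × 0.7 = 0.14.

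| Switched | Difference, r = 1 | Non-inferiority declared | Difference, r = 0.5 | Non-inferiority declared |
|---|---|---|---|---|
| 0% | 0.20 | 5.0% | 0.20 | 5.0% |
| 10% | 0.18 | 8.2% | 0.19 | 6.4% |
| 20% | 0.16 | 12.6% | 0.18 | 8.2% |
| 30% | 0.14 | 18.6% | 0.17 | 10.2% |
| 40% | 0.12 | 26.1% | 0.16 | 12.6% |
| 50% | 0.10 | 34.8% | 0.15 | 15.4% |

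**Per-protocol, deficit equal in all patients.** Let *d* be the prognostic HAQ difference, switchers minus non-switchers. Removing switchers from one arm lowers that arm's mean by s × d, so the difference is 0.2 − s × d. At s = 30%, 51 × 0.7 ≈ 36 patients remain against 51, and SE = 0.4 × √(1/36 + 1/51) = 0.0871.

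| d | Difference | Non-inferiority declared |
|---|---|---|
| +0.4 | 0.08 | 39.1% |
| +0.2 | 0.14 | 16.8% |
| 0 | 0.20 | 5.0% |
| −0.2 | 0.26 | 1.0% |
| −0.4 | 0.32 | 0.1% |

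**Per-protocol, deficit concentrated in discordant patients.** Suppose the deficit is 0.1 in non-switchers and 0.2 overall. At s = 30% the deficit in switchers is (0.2 − 0.7 × 0.1)/0.3 = 0.43. Per-protocol then declares non-inferiority 30.7% of the time at d = 0, 80.6% at d = +0.4 and 3.1% at d = −0.4.

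**Per-protocol power with no true difference and d = 0.** It falls from 80.6% to 73.7% at 30% switched and 66.0% at 50%.

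**The case against.** A reader might infer that both analyses lean toward declaring HandScan non-inferior. The documents do not support that for the per-protocol set. Its bias changes sign with the prognosis of switchers, and the section on under- and overtreatment allows discordance in either direction without giving the mix.

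Two statements make worse HAQ among switchers plausible. The outcome rationale says "DAS-based remission criteria have a relatively high risk of false negative classification of remission" because of non-inflammatory pain, and the Discussion concedes that HandScan sees only hands and wrists. But the first explains why DAS remission was not chosen as the primary outcome; it does not describe switchers. Table 1 also excludes painful conditions that might interfere with pain evaluation, which reduces that group. The planned model adjusts for baseline HAQ and DAS28, which would absorb part of any prognostic difference, and the lost power works against a non-inferiority claim.

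The ITT objection also carries weight. The override is a pre-specified, blinded part of the HandScan arm, and ITT estimates that strategy validly. Under that reading the higher rates in the first table are not errors. Full restoration is the extreme case, because a late switch leaves less time to recover.

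Finally, extra sensitivity analyses and the rule for combining ITT and per-protocol may stand in a SAP that is not shown. That does not excuse the per-protocol definition, which this article fixes.

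**Conclusion.** The one-sided exclusion follows from the text and needs no assumption. The per-protocol set is a selective comparison whose bias may run either way: at 30% switched, the chance of declaring non-inferiority at a true deficit of 0.2 is 16.8%, 5.0% or 1.0% for d of +0.2, 0 or −0.2. It therefore neither confirms nor contradicts ITT.

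ITT stands for HandScan guidance with the DAS override. Only for a claim about HandScan guidance alone does it dilute the deficit, with the 5% error rising to 8% to 35% under full restoration or 6% to 15% under half restoration. These ranges rest on an assumed switch share of 10% to 50% and an unadjusted test.

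**What to change.** 1. Delete the switch clause from the per-protocol exclusion and keep the exclusion for major protocol violations. The switch is a step the protocol itself mandates, not a departure from it. The revised set will carry the same dilution as ITT, so it checks adherence to the override strategy and not HandScan guidance alone.
2. As a sensitivity analysis, derive the three-consecutive-discordance flag in both arms from the monthly HandScan and DAS44 data, and treat flagged patients identically in both arms. State that it is supportive only: the flag arises after randomization and depends on the guidance received, and excluding flagged patients leaves those in whom the two methods mostly agree.
3. Word the non-inferiority conclusion as applying to HandScan guidance with a DAS-based override.

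Treatment, visits and the switch rule stay unchanged. The cost is one derived variable and a narrower claim. Settle this before unblinding, so that the handling of switchers is not chosen after the results are seen.
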